## Methods/design

### Study design

The PROMOTE study (High-protein and resistance-training combination in overweight and obesity) is an 8-week randomized parallel controlled trial followed by a 24-week observational follow-up study. A 48-week supplementary follow-up study will be carried out if necessary. The enrolled participants will be randomly assigned to the conventional low-fat diet group, the high-protein diet group, or the high-protein and resistance-training combination group, and changes in body weight, body fat and metabolic indexes will be compared between the three groups in the short term (8 weeks), the medium term (24 weeks) and the long term (48 weeks). The efficacy of the high-protein and conventional low-fat diets on weight loss, fat loss and improvement of various metabolic indexes will be evaluated and compared with the efficacy of the resistance training and high-protein diet combination. After 8 weeks of intervention, the participants will be strongly recommended to continue their diet and exercise plans until the achievement of individualized weight loss goals. During the following 24 or 48 weeks of observation, the participants’ diet management knowledge will be tested, their self-efficacy evaluated, and the proportion who continued to adhere to the plans will be observed. Finally, the relationship between diet management knowledge, self-efficacy and weight loss will be explored (Fig. 1).

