A high-protein diet can provide sufficient satiety and food taste to resist the hunger caused by calorie restriction and can therefore increase compliance. Compared with a high-carbohydrate diet, a high-protein diet has a more significant thermic effect, which increases energy consumption [16]. A high-protein diet combined with resistance training can reduce the loss of fat-free body mass during weight loss and maintain a relatively high basal metabolic rate. It can also develop good dietary management habits and improve self-efficacy in the initial weight loss stage. This improvement in self-efficacy comes from enthusiasm for diet intake management and exercise. People with low self-efficacy tend to be more likely to give up and regain weight [17]. There have been a few international studies on short-term weight loss and long-term weight maintenance linked to a high-protein diet [18], but high-quality research on the effect of a high-protein diet on weight loss in the Chinese population is very limited [19]. More importantly, there are only a few international and Chinese studies on the role of resistance training in medium- and long-term weight maintenance, and the results are inconsistent [20–23]. We hypothesized that resistance training combined with a high-protein diet would result in similar short-term weight loss but better long-term weight maintenance than either a conventional low-fat diet control or a high-protein diet alone.

The objectives of this study were therefore: 1) to verify that a high-protein diet has a similar short-term weight loss effect as a traditional low-fat diet; 2) to verify that a high-protein diet combined with resistance training can achieve better medium- and long-term weight maintenance; and 3) to explore whether the improvement in self-efficacy and the ability for diet management during weight loss is a predictive factor for medium- and long-term weight maintenance.

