#### Intervention period

The participants’ baseline data will be collected, including body weight, body fat percentage and fat-free mass (using the Tanita TBF-300A Body Composition Analyzer, Tanita Europe, UK), waist circumference, hip circumference, systolic and diastolic blood pressure (Omron sphygmomanometer, Omron Healthcare Limited, Milton Keynes, UK), and a blood sample for the determination of blood glucose, blood lipids, renal function and insulin level. These will be collected in the morning after an 8-h fast.

During the 8-week intervention, the participants will receive dietary guidance, which varies by group, and prepare their own food following advice from the dietician. Participants in the resistance training group have to take part in resistance training at least three times a week. During the 8 weeks, the participants will receive face-to-face visits in weeks 2, 4 and 6, and their body weight, waist circumference, hip circumference, and systolic and diastolic blood pressure will be measured during each visit. The participant will receive telephone calls during weeks 1, 3, 5 and 7. During both visits and telephone calls, dietary and exercise guidance will be provided and recorded, and the MyFitnessPal diet inputs will be checked and recorded in written case report forms. The participants will also receive a face-to-face visit at the end of the 8-week intervention, and their body weight, body fat percentage and fat-free weight, waist circumference, hip circumference, and systolic and diastolic blood pressure will be measured, and blood samples taken for the determination of blood glucose, blood lipids, renal function and insulin levels. The participants’ self-efficacy will be investigated using the General Self-Efficacy Scale [24], and the diet management knowledge will be evaluated using a self-designed questionnaire.

During the intervention period the participants will not be allowed to add anything to their agreed intake (such as snacks and drinks) or to change their diet. If the participants wish to change their main meal for a particular reason (such as a social event), the investigator will be consulted by telephone to decide on the remedial measures required (such as reduction of calorie intake the next day). Any changes will be recorded using the MyFitnessPal record.

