#### Follow-up period

During the follow-up period, participants will no longer be required to continue with their diet and training plan, although this will be strongly recommended by the investigators until the achievement of individualized weight loss goals. The participants will receive a telephone follow-up every 4 weeks when their body weight and waist circumference will be measured by the participants themselves and recorded by the investigators. Face-to-face visits will be also carried out at the end of the 24-week observation period. Body weight, body fat percentage and fat-free mass, waist circumference, hip circumference, and systolic and diastolic blood pressure will be measured, diet will be investigated, and blood samples will be taken for the determination of blood glucose, blood lipids, renal function and insulin levels.

During the baseline period and throughout the trial the participants will be asked to maintain a flexible diet, pay attention to the type, quantity and weight of their food and liquid intake, and use the smartphone application MyFitnessPal to record their daily diet in detail. This is a reliable way to track diet [25–27]. Throughout the study, the investigators will use WeChat, telephone or MyFitnessPal to monitor and guide the participants on diet and training, ensure strict compliance with plans, and provide extra guidance to anyone with poor compliance. Participants with poor compliance will be allowed to continue to participate but will be warned about the importance of compliance. Diet will be evaluated using the professional diet analysis software Nutritics (Nutritics Ltd., Dublin, Ireland). The participants’ daily calorie intake will be assessed using the Katch-McArdle formula, which is based on the resting daily energy expenditure (RDEE; 370 + (21.6 × lean body weight in kg)) and adjusted for exercise needs and nonexercise adaptive heat generation [28]. The calorie intake assessment will ensure that participants have a negative calorie balance of 500–700 kcal per day during the study period, so the daily recommended energy intake (kcal) will be 1.2 (or 1.3) × RDEE − 500 (or 700). Daily protein intake in the high-protein diet group = fat-free mass × 1.5–2.0 (g), and the daily protein intake in the conventional protein diet group = fat-free mass × 0.8–1.2 (g).

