#### Outcomes

The primary outcome is body weight change at week 8 and week 24 compared with the baseline level.

Secondary outcomes include:
Change in body fat percentage at weeks 8 and 24 compared with the baseline levelChange in waist circumference at weeks 8 and 24 compared with the baseline levelThe proportion of participants who have successfully lost weight and been nonobese (defined as BMI <24 kg/m^2^) at weeks 8 and 24Diet management ability and weight loss perseverance at weeks 8 and 24Change in self-efficacy at weeks 8 and 24 compared with the baseline levelCompliance with the original diet plan at weeks 8 and 24Change in fasting blood glucose at weeks 8 and 24 compared with the baseline levelChange in fasting insulin level at weeks 8 and 24 compared with the baseline levelChange in blood pressure at weeks 8 and 24 compared with the baseline levelsIncidence of adverse events

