## Discussion

Generally speaking, an energy imbalance causes obesity or overweight. Only a negative energy balance can result in weight loss. To lose weight, therefore, people require an energy intake that is always lower than their energy consumption [29]. Diet and exercise are ways to control energy intake and consumption, and the basic strategy to lose weight is diet control, exercise, or a combination of the two. In addition to calorie restrictions, a low-fat diet is also considered to be important in weight loss because different nutritional ratios have different effects on satiety, fat-burning and maintaining fat-free mass (muscle) with metabolic activity. As well as aerobic exercise, resistance training has been found to reduce fat, which plays an important role in maintaining fat-free mass and high metabolic activity.

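### Fat loss is to be compared between arms, but the only fat outcome is body fat percentage, which falls further for the same fat loss in an arm that keeps fat-free mass

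*Protocol article*

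**What the plan says.** The Study design section of the protocol article sets out the comparison: "changes in body weight, body fat and metabolic indexes will be compared between the three groups". It continues: "The efficacy of the high-protein and conventional low-fat diets on weight loss, fat loss and improvement of various metabolic indexes will be evaluated", with the combination of diet and resistance training as the comparison.

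The Outcomes section gives the fat variable as "Change in body fat percentage at weeks 8 and 24", measured against baseline. Waist circumference is also listed, but it is only a proxy for fat. Neither fat mass in kg nor fat-free mass appears in the list.

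On mechanism, the Background states: "A high-protein diet combined with resistance training can reduce the loss of fat-free body mass during weight loss". The Discussion says of resistance training that it has an effect "which plays an important role in maintaining fat-free mass and high metabolic activity".

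The components are collected. The Intervention period section has "body weight, body fat percentage and fat-free mass (using the Tanita TBF-300A Body Composition Analyzer" at baseline and the same three quantities at week 8. Table 1 schedules body fat percentage and lean body mass at V2 and V10. For the visit that closes the observation period, the Follow-up period section states: "Body weight, body fat percentage and fat-free mass, waist circumference, hip circumference, and systolic and diastolic blood pressure will be measured".

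**The concern.** Fat loss is an amount, whereas body fat percentage is a ratio of fat to total weight. The two can diverge when fat-free mass changes differently between arms, and that difference is what the protocol expects resistance training to produce. The divergence therefore falls on the contrast between the combination arm and the diet arms.

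At stake is how a secondary result is read. A larger fall in percentage in the combination arm could be reported as more fat lost when part or all of it reflects fat-free mass that was kept. The preservation of fat-free mass, which is the mechanism the protocol proposes, has no outcome of its own to show which explanation applies.

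**Working it through.** The plan gives no figure to reproduce here: no body composition, expected fat-free mass effect or standard deviation (SD). The inputs below are assumptions, and a range follows.

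**Formula.** Body fat % = 100 × (F − f) / (W − f − m), where W is starting weight, F starting fat mass, f fat lost and m fat-free mass lost (negative if gained).

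**Assumed participant.** W = 75 kg and 35% fat, so F = 26.25 kg and fat-free mass = 48.75 kg.

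| Case | f (kg) | m (kg) | Total weight lost (kg) | Body fat % at end |
|---|---|---|---|---|
| A. Diet arm | 4 | 1 | 5.0 | 22.25/70 = 31.79 |
| B. Combination, fat-free mass kept | 4 | 0 | 4.0 | 22.25/71 = 31.34 |
| C. Combination, 0.5 kg gained | 4 | −0.5 | 3.5 | 22.25/71.5 = 31.12 |
| D. Combination, less fat lost | 3.7 | 0 | 3.7 | 22.55/71.3 = 31.63 |
| E. Combination, same weight loss as A | 5 | 0 | 5.0 | 21.25/70 = 30.36 |

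**Equal fat loss.** A − B = 0.45 points and A − C = 0.67 points, although each case lost 4 kg of fat. Against the diet arm's fall of 35 − 31.79 = 3.21 points, that is 14% to 21%.

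**The same gap in kg of fat.** With 1 kg of fat-free mass lost, the diet arm has 47.75 kg left. To match B it would need 22.25 × 47.75/48.75 = 21.79 kg of fat, a loss of 4.46 kg. To match C it would need 22.25 × 47.75/49.25 = 21.57 kg, a loss of 4.68 kg. The artefact therefore looks like 0.46 to 0.68 kg of extra fat loss.

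**Reversal.** In D the combination participant loses 0.3 kg less fat than A and still ends with a lower percentage.

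**When it cannot mislead.** Fat mass equals weight × percentage. From the same starting point, if the combination arm ends at the same or a lower weight with a lower percentage, its fat mass is also lower. E shows this: weight loss equals A, the percentage is lower, and 1 kg more fat really was lost. A misleading result therefore requires the combination arm to lose less total weight.

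**Range.** Over starting weights of 65–85 kg, 30–40% fat and equal fat loss of 3–5 kg, preserving 1.0, 1.5 or 2.0 kg of fat-free mass lowers the percentage further by 0.32–0.61, 0.49–0.92 or 0.66–1.24 points.

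**Chance of a nominally significant artefact.** With 30 per arm, a two-sided 5% test and assumed SDs of change of 1.0, 1.5, 2.0 and 2.5 points, a 0.45-point artefact reaches significance with probability 0.41, 0.21, 0.14 and 0.10. For 0.68 points the probabilities are 0.75, 0.42, 0.26 and 0.18.

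**The case against.** The best defence has four parts.

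- **The data can be split.** Weight, body fat percentage and fat-free mass are measured together at baseline, week 8 and the end of observation. A reader might infer from the outcome list that the trial cannot separate fat from fat-free mass, or cannot answer its own fat-loss question. The documents do not support that: fat mass follows directly from planned measurements. What stands is only that the derived quantity is not a named outcome.
- **The misleading case needs unequal weight loss.** The Background hypothesises similar short-term weight loss, and at equal loss the percentage has the right direction. A reader might infer that the combination arm will show a spurious fat advantage; the text supports only that it can. The 1.0 to 1.5 kg shortfall in cases B and C would fall on the primary outcome and be visible there. Similar is not equal, however. With 30 per arm and an assumed SD of weight change of 2 to 3 kg, the 95% half-width for a difference is 2.00 × SD × √(2/30), or 1.03 to 1.55 kg. A shortfall of that size could be reported as similar weight loss alongside a larger fall in body fat percentage.
- **The Study design section is an overview, and the Outcomes section defines its terms.** That is fair, and the two sections do not contradict each other. The list is nevertheless specific, and the variable it fixes is not the amount of fat lost.
- **The consequence is limited.** This is a secondary outcome in an exploratory pilot, none of the three objectives concerns fat loss, and every magnitude above is assumed. All of this stands, and it limits the weight of the point.

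**Conclusion.** The point holds in a limited form. Fat loss is promised as a between-arm comparison, the only listed fat outcome is a percentage, and the protocol expects its denominator to differ by arm. For the same fat lost, the combination arm can show a fall in percentage that is 0.45 to 0.67 points larger when its fat-free mass is 1 to 1.5 kg better preserved, assuming 75 kg, 35% fat and 4 kg of fat lost in both arms. This arises only if that arm loses less total weight. The effect concerns the interpretation of one secondary outcome and leaves body weight as the primary outcome untouched.

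**What to change.** In the Outcomes section, add two secondary outcomes at the same visits as body fat percentage: change in fat mass in kg (body weight minus fat-free mass) and change in fat-free mass in kg. State that any conclusion about fat loss rests on fat mass in kg. Body fat percentage can stay on the list.

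No visit, device or measurement is added. The cost is two more derived secondary outcomes in an exploratory pilot and an update to the outcome list. Naming them in advance also prevents the fat measure from being chosen after the results are seen.

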**Methods/design:**

This is an 8-week randomized parallel controlled trial followed by a 24-week observational follow-up study. A 48-week supplementary follow-up study will be carried out if necessary. The study will be conducted between June 2019 and October 2020. The 90 overweight or obese participants will be randomly assigned to the conventional low-fat diet group, the high-protein diet group and the high-protein diet and resistance training combination group. Primary outcomes are body weight change at week 8 and week 24 compared with the baseline level.

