To achieve successful long-term weight loss, the intervention must effectively improve the individual’s self-efficacy. Improvements in self-efficacy are strongly affected by the management of dietary intake and the enthusiasm for exercise; participants who regain weight are more likely to give up and lose motivation [17]. One of the core requirements of resistance training is to persist, so it may have a better effect on perseverance than traditional aerobic exercises such as fast walking or jogging. In this study, we assumed that resistance training can increase the proportion of subjects who adhere to the original diet (or decrease the degree of noncompliance), and therefore ultimately improve the long-term weight loss effect to avoid regaining weight.

Overweight and obesity are worldwide problems, and the exploration of scientific weight management and weight loss schemes has been an important area of research and has attracted a lot of investment. However, appropriate weight loss and weight maintenance strategies in specific populations (such as different ethnic groups) and social environments are unclear. We hope that the PROMOTE study will provide a basis for obesity management in China and promote the development of exercise- and diet-related studies. These are important to improve nutritional status, promote healthy development, prevent obesity-related diseases, and improve the health and quality of life of the population.

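### Objective 3 is about predicting weight maintenance, but the stated analysis uses weight loss, and every weight outcome still contains the week 0–8 loss

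*Protocol article*

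**What the plan says.** In the Protocol article, the last paragraph of Background gives the third objective as follows: "explore whether the improvement in self-efficacy and the ability for diet management during weight loss is a predictive factor for medium- and long-term weight maintenance". The predictor belongs to the weight-loss phase and the outcome to the time after it.

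The matching analysis is one sentence in Study design: "Finally, the relationship between diet management knowledge, self-efficacy and weight loss will be explored". It names weight loss. It names neither regain nor maintenance, and Statistical analysis adds no model for this objective.

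Under Outcomes, "The primary outcome is body weight change at week 8 and week 24 compared with the baseline level". Self-efficacy is likewise listed as a change from baseline at weeks 8 and 24. No weight outcome starts at week 8.

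Intervention period places the questionnaire at the visit closing the 8 weeks, where week-8 weight is also taken: "self-efficacy will be investigated using the General Self-Efficacy Scale". Diet management knowledge is scored at that visit too; Table 1 marks it at week 8 only, so that table shows no baseline value.

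Weights after week 8 will exist. Follow-up period plans a clinic visit at the end of observation, and before it: "The participants will receive a telephone follow-up every 4 weeks when their body weight and waist circumference will be measured by the participants themselves".

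**The concern.** Weight loss and weight maintenance are different outcomes, and the article's own hypothesis separates them: it expects similar short-term loss but better long-term maintenance in the combination group. A week-24 change from baseline is the week-8 loss minus later regain. A factor related only to the first part will also be related to the total, without saying anything about the second part.

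Timing adds to this. Week-8 self-efficacy is scored when the initial loss has already taken place. Self-efficacy scored during follow-up runs alongside any regain, and the Discussion describes an influence in that reverse direction: "participants who regain weight are more likely to give up and lose motivation". The Discussion also assumes that resistance training improves adherence and long-term weight, so a relation that ignores randomized group could carry the group effect.

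At stake is the answer to one of three stated objectives. Self-efficacy could be reported as a predictor of maintenance, and taken up as a target for later programmes, on an association that reflects only the initial loss.

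**Working it through.** The plan gives no correlation, standard deviation, significance level or error rate for objective 3, so there is no figure to reproduce. Its only usable number is the sample size, 3 × 30 = 90: "The 90 overweight or obese participants will be randomly assigned".

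**Notation.** S is the week 0–8 change in self-efficacy, L8 the loss at week 8, G the regain from week 8 to the follow-up weight, and L24 = L8 − G the loss from baseline.

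**Assumptions (none is in the documents).** r = corr(S, L8), from 0 to 0.4; k = SD(G)/SD(L8), from 0.5 to 1.5; c = corr(L8, G), 0 or 0.3; a two-sided 5% correlation test; n = 90, or 72 after 20% loss (90 × 0.8). S is set uncorrelated with G, so there is no true link to regain.

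**Step 1, induced correlation.** Since cov(S, G) = 0, cov(S, L24) = cov(S, L8), and

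corr(S, L24) = r / √(1 + k² − 2ck).

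With k = 1 and c = 0:
- r = 0.2 gives 0.2/√2 = 0.141
- r = 0.3 gives 0.3/√2 = 0.212

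**Step 2, chance of a significant result (Fisher z, n = 90, √87 = 9.327).**
- r = 0.2: atanh(0.141) × 9.327 = 1.33; Φ(1.33 − 1.96) ≈ 26%
- r = 0.3: atanh(0.212) × 9.327 = 2.01; Φ(2.01 − 1.96) ≈ 52%

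**Step 3, simulation over all k and c (4,000 trials per setting).** Share of trials with p < 0.05 and no link to regain:

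| r | week-8 loss, n = 90 | week-24 loss, n = 90 | week-24 loss, n = 72 |
|---|---|---|---|
| 0 | about 5% | about 5% | about 5% |
| 0.1 | about 15% | 8–16% | 7–14% |
| 0.2 | about 47% | 18–49% | 16–41% |
| 0.3 | about 83% | 37–84% | 28–76% |
| 0.4 | about 98% | 56–98% | 46–95% |

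At k = 1, c = 0, n = 90 the simulation gives 27% (r = 0.2) and 53% (r = 0.3), in line with step 2.

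**Step 4, regain from week 8 as the outcome.** Without adjustment for L8, rejection is 4–6% in every setting of step 3. With adjustment it stays near 5% when c = 0. When c = 0.3, the result depends on what no link means:

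- *S uncorrelated with G overall.* The partial correlation given L8 is −rc/√((1 − r²)(1 − c²)). At r = 0.3 this is −0.09/0.91 = −0.099. The adjusted model rejects in about 9%, 15% and 25% of trials at r = 0.2, 0.3 and 0.4.
- *G depends on L8 only, with no direct role for S.* Then corr(S, G) = rc, for example 0.4 × 0.3 = 0.12. The unadjusted model rejects in 9–21% over r = 0.2 to 0.4, while the adjusted model stays at 4–5%.

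Neither version is right under both definitions, so both are needed.

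**The case against.** The strongest reply is that the article fixes no test here. The sentence in Study design is a one-line summary of something to be explored. It gives no time pairing, pooling rule, covariates or threshold, the study is labelled an exploratory pilot, and the model may sit in a fuller document. Relating week-8 self-efficacy to later weight would fit the sentence as well as a same-visit correlation. This stands, and it limits the point: what can be criticized is the outcome named, not an unstated model.

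A second reply is that the article uses weight loss loosely. The Discussion speaks of long-term weight loss and avoiding regain almost as one thing, and the preceding sentence in Study design concerns the observation period. That makes week-24 change the fair reading, but it does not cure the problem, because that change is still counted from baseline.

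A reader might infer that the trial will often report a false predictor. The documents do not support this. It requires self-efficacy gain to be correlated with initial loss, and no value is given. Nor do they state that losing weight raises self-efficacy: Background traces the gain to enthusiasm for diet management and exercise, and says that low self-efficacy leads to regain, which is the forward direction. Intervention period gives no order for weighing and questionnaire within the visit.

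**Conclusion.** The point holds as a mismatch between objective and outcome. Objective 3 concerns maintenance, the stated analysis concerns loss, and no listed outcome separates later weight change from the week 0–8 loss. Followed as written, the analysis can answer a different question.

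Its size is conditional. There is no inflation at r = 0 and little at r = 0.1; it becomes substantial from about r = 0.2. These rates rest on assumed correlations, SD ratios and a 5% test, and should be read as a range of what could happen, not as a forecast. Because the objective is exploratory and the trial a pilot, this is a correction worth making before analysis; it does not affect the primary comparison.

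**What to change.** Replace the last sentence of Study design with wording such as: *Objective 3 will be explored by relating the change in self-efficacy from baseline to week 8, and diet management knowledge at week 8, to weight change from week 8 to the end-of-follow-up face-to-face visit, adjusted for randomized group and baseline weight. Results will be reported both with and without adjustment for weight change from baseline to week 8. Associations with weight change over the same period, or with self-efficacy measured during follow-up, will be reported as concurrent and not as prediction.*

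Diet management knowledge must stay in the sentence because objective 3 names it. It enters as a week-8 score because Table 1 schedules no baseline measurement.

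The cost is small. The visits and measurements needed are already planned, a few covariates are added, and the association will probably be smaller than a concurrent correlation would show.
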